### Statistical analysis

Data analysis will be conducted as intention-to-treat. Missing data will be imputed using multiple imputation technique [71]. All analyses will be performed using statistical software such as IBM SPSS or R. For group comparisons of individual variables, categorical variables will be analyzed using chi-squared tests, and continuous variables will be analyzed using t-tests or Mann-Whitney U tests (for two-group comparisons) and F-tests or Kruskal-Wallis tests (for more than 2 groups). The primary statistical analysis will be a repeated measures logistic regression model for the dichotomized output variable “normal mood yes/no” (GHQ-28 < 5 versus GHQ-28 ≥ 5) with two measurements for each patient (i.e. one at 6 months and one at 12 months), with one binary input variable specifying group allocation. Independent variables will include demographic variables, stroke type and severity measurements, rehabilitation service use and relevant medical variables. Medical and demographic variables will be included in the data analysis model to control for group differences at baseline. Secondary analyses, e.g. sub-group analyses, will be conducted with primary, secondary and process outcomes. The psychometric properties of GHQ-28 will be examined to confirm stability of dimensions in a Norwegian general stroke population across time points. All statistical tests will be performed as two-sided tests with a significance level of 0.05.

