### Sample size calculations

The study’s sample size was calculated based on the primary outcome measure GHQ-28, which has been used in a comparable trial [31, 32]. Following Watkins et al.’s results, we deemed an odds ratio of 1.6 or higher between-groups (intervention/control) with normal mood after 6 and 12 months to be clinically relevant. The calculations are based on a repeated measures logistic regression model for the output variable “normal mood” (GHQ-28 < 5) with two measurements for each patient (i.e. one at 6 months and one at 12 months), with one binary input variable specifying group allocation. Based on 80% power across both time points, the calculated sample size of this study is 300 participants, 150 in each arm of the study. To allow for a 10% dropout rate, we have inflated the number to 330 participants in total.

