#### Process evaluation

The process evaluation of this study is guided by the process evaluation framework outlined by the MRC Population Health Sciences Research Network (PHSRN) [72]. As part of this evaluation, 15–20 participants from the intervention and control groups are invited to participate in individual qualitative interviews after study completion (12 months post stroke). The purpose of these interviews is to gain an in-depth understanding of the participants’ experiences with the adjustment process following the stroke, and their experiences with participating in the intervention or control group and assessment interviews. The interview approach is based on Ricoeur’s phenomenological hermeneutics [73] and the data will be analyzed according to Ricoeur’s interpretation theory [74].

Post-intervention focus groups will be conducted with intervention personnel following the completion of all intervention programs. The purpose of the focus groups is to ascertain an in-depth understanding of the intervention personnel’s experiences with delivering the intervention, their impression of participant responsiveness to the intervention, and to uncover potential threats and facilitators to implementation adherence fidelity.

Focus group interviews with data collectors conducting the data collection interviews will be conducted following completion of all data collection. The purpose of the focus group interviews will be to gain an in-depth understanding of the data collection interviews from the data collectors’ perspective and to assess the suitability of the chosen outcome measures. Thematic content analysis will be applied to the focus group interview data [75].

Detailed enrolment records, attrition protocol, and intervention protocols are logged to facilitate quantitative analysis of implementation fidelity and intervention adherence [76, 77]. Descriptive statistical analyses will be applied to the quantitative data with the purpose of describing the study’s implementation adherence. Furthermore, quantitative data from these protocols will be used to construct an independent variable of intervention adherence (fidelity) to be included in the outcome analyses of the study.

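### The text fits both a group-only and a covariate-adjusted primary test, and the adjusted version as written admits post-randomisation service use and covariate choice by observed imbalance

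*Protocol article*

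**What the plan says.** The Sample size calculations section sizes the trial on a repeated measures logistic regression for normal mood at 6 and 12 months, "with one binary input variable specifying group allocation. Based on 80% power across both time points". No covariate appears there.

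The Statistical analysis section names the same type of model as the primary analysis, repeats the phrase about group allocation and runs straight on into covariates: "with one binary input variable specifying group allocation. Independent variables will include demographic variables, stroke type and severity measurements". In full, the covariate sentence reads "Independent variables will include demographic variables, stroke type and severity measurements, rehabilitation service use and relevant medical variables", and the one after it "Medical and demographic variables will be included in the data analysis model to control for group differences at baseline". Secondary and subgroup analyses come only after these sentences.

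Three other places bear on the covariates:

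- Table 1 files rehabilitation services under medical information, and Table 2 schedules medical information at enrolment, at baseline (t1) and again at 6 and 12 months (t2, t3).
- The Control group section says that data on rehabilitation services are collected in both arms to control for variation in usual care.
- The Process evaluation section plans to "construct an independent variable of intervention adherence (fidelity) to be included in the outcome analyses of the study", without saying which outcome analyses are meant.

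**The concern.** The confirmatory test should be identifiable from the plan before anyone sees results. Here an analyst who fits group alone and one who fits group plus covariates can each point to a sentence in support. The two fits give different p-values from the same data, so the conclusion on the primary hypothesis may turn on which sentence is followed.

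Two features of the adjusted version add to this. First, adjusting in order to deal with group differences at baseline suggests that variables may be chosen after looking at the imbalance, and the closing category of relevant medical variables is open-ended. Second, rehabilitation service use measured at 6 or 12 months is itself something the intervention may change. Conditioning on it can remove part of the effect, or mix it with the reasons why patients sought services.

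**Working it through.** **1. The plan's own figure.** Inputs from the article: odds ratio 1.6, 80% power, two-sided 0.05, two measurements per patient, 150 per arm. The control rate and the correlation between visits are not given and are assumed here. Take a control rate p1 = 0.55 and correlation ρ = 0.

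- Control odds 0.55/0.45 = 1.2222; times 1.6 = 1.9556; so p2 = 1.9556/2.9556 = 0.66165 and the difference is 0.11165.
- Observations per arm = [1.960·√(2·0.6058·0.3942) + 0.8416·√(0.55·0.45 + 0.66165·0.33835)]² / 0.11165² = (1.3545 + 0.5778)² / 0.012466 = 299.5, rounded up to 300.
- Patients per arm = 300 × (1 + ρ)/2 = 150, so 300 in total; 300 × 1.10 = 330.

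The figure of 300 can therefore be reached with group as the only input, which agrees with the section's description. It does so only near ρ = 0 (ρ = 0.5 gives 450 at the same rate). That is a separate matter and nothing below depends on it.

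**2. The model wording side by side.**

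| Place | Input variables named |
|---|---|
| Sample size calculations | group only |
| Statistical analysis, primary-model sentence | group only, same phrase |
| Statistical analysis, next two sentences | demographic, stroke, service-use and medical variables |

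No sentence says that the third row extends the second, or that it describes a supporting model.

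**3. How often the two tests disagree.** Two simulations, each with 300 patients, two binary visits, about 50% normal mood in controls, and logistic regression with patient-clustered standard errors. Covariate number and strength and between-patient variance are assumed.

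*Setting A:* 10 baseline covariates with total logit variance 0.5, 1 or 2; patient variance 2; true effect giving an unadjusted odds ratio of about 1.56; 2,000 trials with an effect and 3,000 without per setting. The tests gave opposite verdicts in 10%, 14% and 20% of trials. Power was 62 to 64% unadjusted and 67 to 74% adjusted. With no effect, at least one test was significant in 6 to 9%, against about 4 to 6% for either alone.

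*Setting B:* 5 baseline covariates with total logit SD 0.5, 1.0 or 1.5; patient SD 1; 1,000 trials per cell.

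| Covariate SD | Conditional OR | Significant, group only | Significant, adjusted | At least one | Opposite verdicts |
|---|---|---|---|---|---|
| 0.5 | 1.6 | 53.9% | 56.8% | 60.2% | 9.7% |
| 1.0 | 1.6 | 43.9% | 51.2% | 55.5% | 15.9% |
| 1.5 | 1.6 | 32.5% | 47.7% | 51.2% | 22.2% |
| 0.5 | 1.0 | 5.3% | 6.1% | 7.0% | 2.6% |
| 1.0 | 1.0 | 6.5% | 6.4% | 9.3% | 5.7% |
| 1.5 | 1.0 | 5.3% | 4.3% | 7.3% | 5.0% |

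Consistency check: opposite verdicts = 2 × (at least one) − group only − adjusted; for the second row, 2 × 55.5 − 43.9 − 51.2 = 15.9. At a conditional odds ratio of 2.0, where adjusted power is 81 to 88%, opposite verdicts occurred in 4%, 14% and 20%. The Monte Carlo standard error is at most about 1.6 points, and about 0.9 points for the 9.3%.

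**4. Service use.** The Statistical analysis section does not say at which time point service use enters the model. Table 2 has it recorded before and after randomisation, and the stated aim of controlling for usual care points to services received during follow-up. The article gives no data from which the size or direction of the resulting distortion could be computed.

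**The case against.** The strongest reply is that the section describes one adjusted model. Its primary-model sentence names the outcome, the visits and the treatment term; the covariates follow at once; they go into a single, definite data analysis model; and only then do secondary analyses begin. On that reading the phrase about one binary variable merely says how treatment is coded. This is plausible, and it means the article should not be read as declaring two rival primary analyses. It does not settle the matter, because the same phrase describes a complete model without covariates in the sample-size section.

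It is also fair that sizing on a group-only model and then adjusting is normal practice, and in these simulations adjustment raised power. A reader might infer that the sample size is invalidated by the adjustment; it is not. The exact covariate list may properly sit in an analysis plan that is not shown, so its absence is no finding.

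A further tempting inference is that 1.6 is a marginal threshold and that an adjusted odds ratio must overstate the effect against it. The documents do not support this. The article says "we deemed an odds ratio of 1.6 or higher between-groups (intervention/control" is clinically relevant, following a comparable trial, but not whether that ratio was unadjusted. Nor does it say whether the repeated measures model is marginal or has a patient random intercept. In setting A's marginal fit the adjusted odds ratios were 1.61, 1.66 and 1.74 against about 1.56. In a random-intercept fit with the same variances (n = 60,000, true conditional odds ratio 2.01), group-only estimates were 2.02, 2.00 and 2.00 and adjusted estimates 2.02, 2.00 and 2.02, so the drift disappears. Discordant p-values remain possible under either model.

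Finally, a reader might take the adherence variable as part of the primary model. The Process evaluation section does not say so.

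**Conclusion.** The point holds as an ambiguity in the confirmatory model, together with two weaknesses in the adjusted version: it does not exclude service use measured after randomisation, and it gives a reason for adjustment that invites selection on observed imbalance.

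The 10 to 22% disagreement applies to true effects near the planned size, with assumed covariate strength, patient variance and a control rate near 50%. The simulated power there is below the stated 80%, and disagreement can fall to about 4% when the effect is larger and the covariates weak. The 6 to 9% false-positive rate arises only if both tests are run and the favourable one reported, so the inflation over 5% is modest. The service-use problem cannot be sized from the article, and it would not arise if only pre-randomisation use were meant. The point is worth correcting because it concerns the single primary test and the correction is cheap.

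**What to change.** In the Statistical analysis section, state one primary model: group plus a set of covariates measured before randomisation, fixed before unblinding and not selected on observed baseline differences. Reword the phrase about one binary variable so that it describes the treatment term and not the whole model. Remove post-randomisation rehabilitation service use from that model; it can be described by arm or used in a labelled supporting analysis. Label the group-only model as a sensitivity analysis. In the Sample size calculations section, note that the calculation was made for the group-only model.

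Stating whether the model is marginal or has a patient random intercept would make the reported odds ratio interpretable. Reporting a standardised effect as well is optional.

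The cost is a few sentences, with no new data or patients. The Trial status section has data collection running to the end of June 2018, so on the article's own timetable the wording could be settled before results were known. What is given up is follow-up service use as an adjuster in the primary model.

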### Control group

The control group receives treatment as usual and no intervention beyond participation in the assessment interviews at 1, 6, and 12 months. As participants are recruited from a variety of settings (acute stroke care and rehabilitation units), we anticipate some variation in the usual care provided. Provision of rehabilitation services is the responsibility of the community health care services in Norway, and this adds to the anticipated variability in services. Systematic psychosocial rehabilitation and support is not implemented in community health care services in Norway. However, adoption of the National stroke treatment guidelines in the acute phase of stroke (based on international stroke treatment guidelines) is high in Norway. To control for the potential variability in “usual care”, we collect data on the types of rehabilitation services received in both arms of the study.

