Sense of coherence	Sense of Coherence scale (SOC-13)	Self-report questionnaire, 13 components, measuring the main concepts in the SOC theory; coherence, meaningfulness and manageability. 13 items scored on a Likert scale, ranging from 1 to 7. Higher scores indicate a stronger SOC.
Depression and anxiety	The Yale Brown single item questionnaire (Yale)	One yes/ no question
Fatigue	Lee’s Fatigue scale-5 (Lee-5)	A 0–10 scale assessing symptoms of fatigue
Fatigue	Fatigue Questionnaire-2 (FQ-2)	One yes/ no question, If yes; length of symptoms.
Demographics		Age, gender, ethnic background, education, type of work/studies, marital status, living condition, family/network, place of living (urban/rural)
Medical information		Time of stroke, type / localization of stroke, type of medical treatment after stroke, medication, other chronic diseases, earlier depression / mental disorders, rehabilitation services provided, type and amount of health care/practice assistance provided in the community.
Stroke severity	National Institutes of Health Stroke Scale (NIHSS)	A questionnaire used by healthcare providers to objectively quantify the impairment caused by a stroke.
Aphasia	The Ullevaal Aphasia Screening Test (UAS)	Screening for aphasia.

All instruments will be administered at T1 (at 1 month post-stroke and before randomization and potential initiation of the intervention), at T2 (6 months after stroke, approximately two weeks after the end of the intervention), and at T3 (12 months after stroke / 6 months after the end of the intervention). The instruments will be administered by data collectors with a health care background (RN and OT) using a personal interview format. The assessor is blinded to group allocation at each data collection point. At T0 (at hospital / rehabilitation unit) medical information about the stroke and stroke severity (NIHSS-score) will be collected. Data and all appropriate documentation will be stored for a minimum of 5 years after the completion of the trial, including the follow-up period. The Standard Protocol Items: Recommendations for Interventional Trials (SPIRIT) Flow diagram showing the schedule for enrolment, interventions and assessments is provided in Table 2.

**Table 2 Tab2:** Schedule of enrolment, intervention, and assessments (SPIRIT)

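### The covariate list for the outcome model includes rehabilitation service use without limiting it to a pre-randomisation value; if the sessions change service use, the group odds ratio may no longer estimate the total randomised effect

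*Protocol article*

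**What the plan says.** All places are in the protocol article.

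- **Statistical analysis, the model.** "The primary statistical analysis will be a repeated measures logistic regression model for the dichotomized output variable", namely normal mood (GHQ-28 below 5) at 6 and 12 months. The same sentence gives the model a single binary predictor, the allocated group. Sample size calculations describes the same group-only model.
- **Statistical analysis, the covariates.** The next sentence reads: "Independent variables will include demographic variables, stroke type and severity measurements, rehabilitation service use and relevant medical variables". It does not say whether this is the primary model or a further adjusted one, and gives no time point for service use.
- **Statistical analysis, the reason.** "Medical and demographic variables will be included in the data analysis model to control for group differences at baseline". No separate reason is given there for service use.
- **Statistical analysis, the principle.** "Data analysis will be conducted as intention-to-treat".
- **Control group.** To control for variation in usual care, "we collect data on the types of rehabilitation services received in both arms of the study".
- **Table 1.** The medical information row includes "rehabilitation services provided, type and amount of health care/practice assistance provided in the community".
- **Table 2.** Medical information is marked at enrolment, t1, t2 (6 months) and t3 (12 months).
- **Outcome measurements.** T1 takes place "at 1 month post-stroke and before randomization and potential initiation of the intervention", so anything first recorded at T2 or T3 is post-randomisation.

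**The concern.** Services received between T1 and T3 come after allocation. Nurses or occupational therapists hold eight sessions on coping, bodily changes and daily life in the same months in which community services are provided, so the sessions could raise or lower service use. Two problems would follow from adjusting for it.

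1. **Mediation.** If the sessions change service use and service use affects mood, holding service use fixed removes that part of the effect.
2. **Collider bias.** Patients with greater unmeasured need are likely to use more services and to have worse mood. If allocation also changes service use, patients with equal service use in the two arms differ in need, and the comparison is no longer protected by randomisation.

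Usual-care variation does not require this adjustment. Randomisation, stratified by centre, already makes the arms comparable on the care they would otherwise have received. At stake is the interpretation of the primary odds ratio, for which the protocol set this target: "we deemed an odds ratio of 1.6 or higher between-groups (intervention/control) with normal mood after 6 and 12 months to be clinically relevant".

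**Working it through.** **Figures in the plan.** None depends on this covariate. The 300 participants (150 per arm) come from a model with group only, and the control rate and within-patient correlation behind that number are not stated. The check therefore has two parts: which variable is meant, and how much it could matter.

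**Step 1: timing.** Table 1 places services under medical information, which Table 2 schedules twice before randomisation and twice after. The Control group section says the data are collected on services received in both arms so that usual care can be controlled for. Care in the two arms is care after allocation. The natural reading is follow-up service use, although the text does not say so outright. The baseline-difference rationale cannot justify it, since services received by 6 or 12 months cannot correct an imbalance at T1.

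**Step 2: illustration under a true null.** All inputs are assumptions; the document gives none. G is group (0/1), U is unmeasured need (SD 1), M is service use, and Y is latent mood at each visit, with normal mood when Y > 0.

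- M = a·G + 0.5·U + error (SD s_M)
- Y = −0.8·U + error (SD s_Y), with no effect of G or M

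At fixed M, the apparent group effect on Y is 0.4·a / (0.25 + s_M²). The residual variance of Y is 0.64 + s_Y² − 0.16 / (0.25 + s_M²). Near 50% normal mood, log OR ≈ 1.6 × apparent effect / residual SD.

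- **Case 1** (s_M = 1, s_Y = 1; correlation of M with U is 0.5/√1.25 = 0.45). Apparent effect 0.32a; residual SD √(1.64 − 0.128) = 1.230. For a = 0.2: 1.6 × 0.064/1.230 = 0.083, OR 1.09. For a = 0.3: 1.6 × 0.096/1.230 = 0.125, OR 1.13. (In SDs of M, these shifts are 0.18 and 0.27.)
- **Case 2** (s_M² = 0.75, s_Y = 1; correlation 0.5). Apparent effect 0.4a; residual SD √1.48 = 1.217. For a = 0.2: 1.6 × 0.08/1.217 = 0.105, OR 1.11. For a = 0.3: 1.6 × 0.12/1.217 = 0.158, OR 1.17.
- **Case 3** (s_M² = 0.75, s_Y = 0.6). Residual SD √0.84 = 0.917. For a = 0.2: 1.6 × 0.08/0.917 = 0.140, OR 1.15. For a = 0.3: 1.6 × 0.12/0.917 = 0.209, OR 1.23. Here need explains 0.64/(0.64 + 0.36) = 64% of the variance of mood, against 0.64/1.64 = 39% in cases 1 and 2.

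Simulation of the two-visit model (150 per arm, cluster-robust logistic regression, 1,500 runs per setting) agrees with these values:

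| Case | Adjusted OR, upward shift | Adjusted OR, downward shift | Type I error, adjusted |
|---|---|---|---|
| 1 | 1.09–1.14 | 0.92–0.88 | about 7–12% |
| 2 | 1.11–1.18 | 0.90–0.85 | about 8–14% |
| 3 | 1.15–1.24 | 0.87–0.81 | about 10–18% |

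Type I error varies by up to about 1 percentage point between runs, since √(0.18 × 0.82/1500) ≈ 0.01. Without M in the model, the OR stays near 1.00 and type I error near 5%. With a = 0, the adjusted OR is also near 1.00. With a weaker link between need and service use (0.2 in place of 0.5), the OR is about 1.04–1.05 and type I error about 6%.

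**Step 3: illustration with a true effect.** This uses a separate simulation of 400,000 patients, with binary service use that improves mood and that the intervention shifts by about 17 percentage points. If use is raised, the group OR goes from 1.56 without service use in the model to 1.40 with it. If use is lowered, it goes from 1.59 to 1.80. With no effect of the intervention on use, the change is 1.48 to 1.48 with unmeasured need, and 1.58 to 1.60 without it. That last gap is only non-collapsibility of the odds ratio.

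**The case against.** The strongest reply is that the primary model may not contain service use at all. Two sections describe it with allocation as the only predictor, and the trial was sized on that model. On that reading, the covariate sentence describes a further adjusted analysis and the primary odds ratio is untouched. This reply stands as far as the wording goes. However, the covariate sentence follows the definition directly and names no other model, and the rationale then speaks of one data analysis model. If the group-only model is primary, the text still has to say so.

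Second, the covariate could be the T1 value, since medical information is also collected before randomisation. A T1 value would be harmless. The Control group section favours the follow-up reading, but the timing remains an inference.

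Third, the bias requires the intervention to change service use. Nothing says that the sessions refer patients or alter provision, and rehabilitation services are the responsibility of community health care. This is correct: with no shift there is no such bias.

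Fourth, the upper end of the illustration needs need to explain 64% of the variance in mood. The stroke severity and medical covariates in the same sentence would also capture part of that need. The range should therefore not be read as a forecast.

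A reader might infer that the primary estimate is certainly biased, or that the intention-to-treat commitment is broken. The document supports neither. All patients can still be analysed as randomised; what may change is the effect being estimated.

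**Conclusion.** The point holds in conditional form. As written, the analysis section permits a post-randomisation covariate in the model that is naturally read as primary, and it leaves two descriptions of that model standing. If the sessions change service use, the adjusted group odds ratio may not estimate the total effect of allocation, and the error can go either way. Under a true null with the assumed inputs, the adjusted odds ratio is about 1.09 to 1.24, or 0.92 to 0.81, with type I error of about 7 to 18%. These distortions matter against a target of 1.6. They shrink to near nothing when need is only weakly tied to service use, and vanish when the intervention leaves service use unchanged. The document does not show which situation applies, and a confirmatory model should not depend on it. The wording should be corrected because it governs the primary estimate. Confidence in the principle is high; confidence in any particular size is low.

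**What to change.** In Statistical analysis:

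1. State which model is primary: group only, or group with named covariates.
2. Delete rehabilitation service use from the primary model, or specify that only its T1 value is used.
3. Restrict every primary-model covariate, including the medical variables, to values recorded at or before T1.
4. Report follow-up service use by arm descriptively, as an account of usual care. Any model containing it should be a labelled exploratory mediation analysis.

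The cost is a sentence or two in the analysis section. No data collection changes, and the sample size is unaffected because it was computed for a group-only model.

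### GHQ-28 is measured before randomisation but is not named as a covariate in the primary model, which gives up precision by an amount the document does not allow one to fix

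*Protocol article*

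**What the plan says.** Outcome measurements fixes the timing of the baseline assessment: "All instruments will be administered at T1 (at 1 month post-stroke and before randomization and potential initiation of the intervention". Table 2 confirms it by marking GHQ-28 at t1, t2 and t3, with allocation following the t1 data collection.

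The primary model is described twice. Sample size calculations gives a repeated measures logistic regression for normal mood (GHQ-28 below 5) "with two measurements for each patient (i.e. one at 6 months and one at 12 months), with one binary input variable specifying group allocation". Statistical analysis opens in the same way ("The primary statistical analysis will be a repeated measures logistic regression model for the dichotomized output variable"), again with group as the one binary input, and then adds: "Independent variables will include demographic variables, stroke type and severity measurements, rehabilitation service use and relevant medical variables". The reason given is: "Medical and demographic variables will be included in the data analysis model to control for group differences at baseline".

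Table 1 itemises what counts as demographics and as medical information. The medical row includes "other chronic diseases, earlier depression / mental disorders, rehabilitation services provided". GHQ-28 is in neither row; it is listed separately under psychosocial well-being.

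**The concern.** The pre-randomisation value of the outcome measure is collected and is an obvious candidate covariate. The covariate classes that the article names do not contain it. The stated reason for adjustment, control of baseline group differences, also points the wrong way. In a randomised trial such differences arise by chance, and covariates are better fixed in advance for their prognostic value than chosen because an imbalance has appeared.

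Two things are at stake. Precision available from data already in hand is not used, and with recruitment closed (Trial status) adjustment is one of the few remaining ways to gain it. In addition, if the arms happen to differ in baseline distress, nothing stated in the primary model corrects for that directly. A lesser point is that a group-only model and a covariate-adjusted model estimate different odds ratios, because the odds ratio is non-collapsible. The article does not say which of them is to be read against its benchmark of 1.6.

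**Working it through.** **Inputs from the article.** Odds ratio 1.6 ("we deemed an odds ratio of 1.6 or higher between-groups (intervention/control) with normal mood after 6 and 12 months to be clinically relevant"), 80% power, 300 participants (150 per arm), two-sided 0.05, and two binary measurements per patient.

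**Inputs not in the article, so assumed.** Control proportion with normal mood (mainly 0.40 to 0.50), correlation between the 6- and 12-month outcomes, and correlation between T1 and follow-up GHQ-28 (r, from 0.2 to 0.7).

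**1. The plan's own figure.** With control rate p0 = 0.50, p1 = 1.6 × 0.5 / (0.5 + 1.6 × 0.5) = 0.8/1.3 = 0.615. For one time point:

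n per arm = (1.96 + 0.84)² × [1/(p0 q0) + 1/(p1 q1)] / (ln 1.6)² = 7.85 × (4 + 4.225) / 0.221 ≈ 292.

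With two measurements correlated at ρ, n per arm is multiplied by (1 + ρ)/2:

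- ρ = 0: 146.1, so 147 per arm and 294 in total.
- ρ = 0.027: 150 per arm, the stated number.
- ρ = 0.5: 219.2, so 220 per arm and 440 in total. Power at 150 per arm is then Φ(0.470/√(8.225 × 0.75/150) − 1.96) = Φ(0.36) ≈ 0.64.

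Over control rates of 0.40 to 0.55, a total of 300 is matched only when ρ is about 0 to 0.04. The article states neither ρ nor the control rate, so its figure cannot be reproduced uniquely. This matters here only because it sets the unadjusted power from which any gain starts.

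**2. Linear approximation to the gain.** Power = Φ(d/√(1 − R²) − 1.96), where d is the unadjusted standardised effect. From 65% unadjusted power, d = 1.96 + 0.385 = 2.345. With R² = 0.25 (r = 0.5), 2.345/0.866 = 2.708 and Φ(0.748) = 0.773, a gain of 12.3 points. With R² = 0.36 (r = 0.6) the gain is 18.4 points. This ignores the dichotomisation of the outcome and so runs high.

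**3. Simulation allowing for dichotomisation.** Latent normal scores at T1, 6 and 12 months; outcome cut to give a marginal odds ratio of 1.6; 300 patients; logistic regression with patient-clustered standard errors; 2000 to 3000 runs per scenario. Control rate 0.50:

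| r (T1/follow-up) | latent follow-up correlation | group only | + continuous T1 | gain | + dichotomised T1 | gain |
|---|---|---|---|---|---|---|
| 0.3 | 0.5 | 0.698 | 0.732 | 3.4 | 0.710 | 1.2 |
| 0.4 | 0.6 | 0.675 | 0.746 | 7.1 | 0.724 | 4.9 |
| 0.5 | 0.7 | 0.652 | 0.750 | 9.8 | 0.718 | 6.6 |
| 0.6 | 0.7 | 0.642 | 0.788 | 14.6 | 0.738 | 9.6 |
| 0.7 | 0.75 | 0.624 | 0.850 | 22.6 | 0.780 | 15.6 |

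A separate run with the latent follow-up correlation held at 0.7 gave gains of about 3, 7, 10 and 17 points at r = 0.3, 0.4, 0.5 and 0.6. In a null scenario (control rate 0.45) the rejection rate was 0.055 to 0.058 with and without adjustment.

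**4. Gain over a model that already holds another prognostic covariate.** Control rate 0.45; the other covariate is correlated 0.3 with follow-up and with T1:

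- r = 0.4: 0.717 to 0.765, 4.8 points.
- r = 0.5: 0.695 to 0.766, 7.1 points.
- r = 0.6: 0.677 to 0.803, 12.6 points.

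With that covariate correlated at 0.4 instead, the gains are 6.2 points at r = 0.5 (0.730 to 0.792) and 10.7 at r = 0.6 (0.722 to 0.829).

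**5. Near-independent follow-up outcomes, as the stated sample size implies.** At r = 0.3, 0.791 to 0.833 (4.2 points); at r = 0.2, 0.793 to 0.812 (1.9 points).

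**The case against.** The covariate sentence names classes and is not expressly closed. This is a journal article, and an unseen analysis plan may already list T1 GHQ-28; nothing in the article excludes it. That stands, so a reader who infers that the trial will certainly leave the baseline value unused goes further than the text. It does not remove the point. The article says which classes enter and why, its own Table 1 places GHQ-28 outside those classes, and the rationale it gives is not the one that would lead to including it.

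A reader might also put a single figure on the lost power, in the low to high teens. The article does not support that. The figure rests on an unstated r of about 0.5 to 0.6 and on comparison with a group-only model. The analysis section plans other covariates, among them earlier depression or mental disorders, and against such a model the gain is smaller.

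A reader might infer that the continuous secondary outcomes will be compared without adjustment, since "continuous variables will be analyzed using t-tests or Mann-Whitney U tests (for two-group comparisons". That sentence is generic: it concerns comparisons of individual variables, goes on to cover more than two groups in a two-arm trial, and is not tied to SAQOL-39 or SOC-13. No such plan is stated.

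Finally, the group-only description in the sample size section may be an ordinary simplification for the calculation, and the analysis section can be read as one adjusted model. That is a fair reading, but the wording leaves it open.

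**Conclusion.** The point holds as one of precision. Baseline GHQ-28 is measured before randomisation and is named in neither description of the primary model, while adjustment is justified by group differences at baseline. In every scenario tried, adding it raised power. The gain over a group-only model runs from about 3 points at r = 0.3, through about 10 at 0.5 and 15 to 17 at 0.6, to over 20 at 0.7, assuming an odds ratio of 1.6, 150 per arm, a control rate of about 50% and a latent follow-up correlation near 0.7. It is less with a dichotomised T1 or with other prognostic covariates present, and only about 2 to 4 points if follow-up outcomes are almost independent and r is 0.2 to 0.3. None of these correlations is in the article.

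A reader might take the omission as a source of bias. It is not: randomisation protects the comparison in expectation, and what is lost is precision and correction of chance imbalance.

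**What to change.** State one primary model: group, visit, continuous T1 GHQ-28, centre (the stratification factor) and a short, fixed list of prognostic covariates measured before randomisation, all included whatever imbalance is seen. Restricting the list to pre-randomisation values also settles how rehabilitation service use is handled, since Table 2 has medical information recorded again at 6 and 12 months.

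Report a marginal (standardised) odds ratio or risk difference beside the conditional odds ratio. In simulation with a marginal odds ratio of 1.6, the conditional one was about 1.76 to 1.85 at r = 0.5 to 0.6, so without the marginal figure the 1.6 benchmark is not comparable.

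Adjusting SAQOL-39, SOC-13 and Yale for their own T1 values would likewise be expected to gain precision.

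The cost is analysis wording only, as the data are already being collected. The one small downside is the conditional scale of the adjusted odds ratio, which the marginal figure addresses.
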